### Consent/ethics

Because inclusion is decided as soon as possible after EMS arrival, informed consent cannot be obtained before enrollment into the study, but deferred consent will be obtained in each case. The RhinoChill device has received CE marking and did not raise any major safety issues in previous studies [23,26]; as such, local Ethics Committees (The Regional Ethical Review Board in Stockholm - reference study number: 2010/383-32; Comité d’Ethique de l’Hôpital Erasme – reference study number: P2012/321; Ethics Committee, University Hospital Hradec Kralove –reference study number: 201204 S24ZP; Commissie Medische Ethiek van Universitaire Ziekenhuizen KU Leuven; reference study number: S54255) approved study in eligible patients who are unable to provide consent prior to their treatment, as they will necessarily be comatose. Ethical consideration for treating subjects without their express consent is in accordance with the World Medical Association Helsinki Declaration of 1964, as revised at the 59th General Assembly in Seoul in 2008. For subjects admitted to the hospital after ROSC, their legal representative will be informed of the study as soon as possible and must approve for data collection and continuation of the study. Subjects who will show neurological recovery will be informed of their study participation and be asked to provide their consent for the use of their data.

### Data safety management

The Data Safety Monitoring Committee (DSMC) is constituted and will review data every 3 months. Given that it is expected that more than half of the patients will die at the scene or during the hospital stay, and that recurrent cardiac arrest at any time is possible with standard care, it is not considered appropriate to report every death to the DSMC as a serious adverse effect. Sites will report all SAEs that occur within 7 days of enrollment directly to DMSC. A “technical device failure” is defined as a failure of the device to perform its intended function when used in accordance with the instructions for use. Technical device failures will be recorded and evaluated for possible untoward effects on the subject. All clinically significant AEs or those that appear to be related to the use of the RhinoChill (i.e., whitening of the nose; epistaxis; mucosal irritation/dryness; para-sinus emphysema) as well as those that could potentially harm the patient (i.e., pleural effusion) will be recorded on the CRF from ROSC through the end of the cooling period.

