### Randomization

Randomization will be carried out in blocks of four and each site will be given sets of sequentially numbered envelopes with randomization assignments provided in a 1:1 manner to distribute to the participating pre-hospital vehicles. Individual envelopes will be placed in each RhinoChill pack at the time of site initiation, and replaced as patients are enrolled. The RhinoChill pack will be carried to every potential subject, and the envelope will be opened once the subject has been qualified as meeting all inclusion and exclusion criteria. Neither EMS or hospital personnel will be blinded to treatment, since the control patients are easily distinguishable from patients undergoing device placement and nasal cooling. However, medical personnel making the final neurological assessment of the patient prior to discharge will be blinded to patient’s group assignment.

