### Study treatment

The resuscitation attempt will follow current guidelines [24] to the greatest extent possible. After airway management (i.e. laryngeal mask or intubation), patients are randomized to early cooling or standard care. In patients randomized to early cooling, the RhinoChill catheters should be placed and cooling initiated immediately. To place the nasal catheters and start cooling takes approximately 1 minute. Cooling should be performed with the oxygen flow set to 40 L/min. There should be no changes to the care received by patients randomized to the control arm. Resuscitation attempts should be continued for at least 30 minutes after EMS arrive on the scene in all patients before deciding that further interventions are futile.

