### Follow-up

Subjects treated with the RhinoChill will undergo rhinoscopic examination of the nasal cavity if it is warranted based on clinical signs of intra-nasal trauma (e.g., bleeding from the nostrils, whitening of the nose or other treatment-related observations). All patients still alive will undergo a neurological examination 72 hours after hospital admission. Neurological status will be classified using the Cerebral Performance Category (CPC) [25]. Subjects will be followed until death or at 90 days. The following data will be recorded concerning their hospital course: date/time subject wakes; date/time subject is taken off ventilator; date/time subject is discharged from ICU; date/time subject dies (if in hospital); date/time subject is discharged from hospital; discharge disposition; CPC at hospital discharge. CPC will be evaluated at 90 days through a telephone interview by an independent physician using the Glasgow Outcome Scale (GOS) and the 15D instrument. If there are difficulties in CPC-classification, the patient will be assessed by a neurologist at an out-clinic visit. Clinically significant serious adverse events will be recorded from the time ROSC is achieved through the earliest of the following three events: death, hospital discharge, or one week following admission. The nature and severity of the adverse event, the relationship to the RhinoChill Device, management and outcome will be recorded on the CRF.

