### Study outcomes

The main objective of this study is to assess the impact on neurological intact survival rates at 90 days of trans-nasal IATH compared to standard treatment. Thus, the primary end-point will be the neurological intact survival rates (i.e. patients with CPC score of 1–2) at 90 days after arrest among all those admitted to the hospital.

Secondary end-points will include:

–Overall survival at 90 days among patients admitted to the hospital.

–Survival and neurological intact outcome at 90 days among all included patients.

–ROSC rate.

–Survival to hospital admission.

–Proportion of patients reaching target temperature (≤ 34° Celsius) within 4 hours of call to dispatcher.

–All adverse events occurring within 24 hours of beginning ALS procedures.

–Serious adverse events (SAE) from the time of patient randomization through the first seven days of hospitalization.

Importantly, in the cases where withdraw of life support is decided due to poor prognosis, the reasons must be clearly stated in the CRF, as well as results of neurological examination or additional tools (i.e. brain imaging, biomarkers, electroencephalography, somatosensory evoked potentials - SSEPs), which are used. No specific recommendation on post-anoxic coma prognostication has been provided in this study.

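### The adverse-event recording rule does not match the all-adverse-events endpoint: minor events attributed to the RhinoChill are recorded whatever their severity, a route that only patients in the cooling arm can meet

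*Protocol article*

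**What the plan says.** Three sections of the protocol article bear on how non-serious adverse events reach the analysis.

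- **Data safety management** gives the recording rule. Its first two routes are "All clinically significant AEs or those that appear to be related to the use of the RhinoChill". The examples attached to the device route are "whitening of the nose; epistaxis; mucosal irritation/dryness; para-sinus emphysema". A third route follows: "as well as those that could potentially harm the patient (i.e., pleural effusion"). All of these "will be recorded on the CRF from ROSC through the end of the cooling period".
- **Study outcomes** lists as a secondary endpoint "All adverse events occurring within 24 hours of beginning ALS procedures". It applies no filter for severity or for relation to the device.
- **Follow-up** provides a nasal examination in one arm only: "Subjects treated with the RhinoChill will undergo rhinoscopic examination of the nasal cavity if it is warranted", the warrant being clinical signs of nasal injury.

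Two further statements give the context. Under Randomization, "Neither EMS or hospital personnel will be blinded to treatment". Under Study treatment, "In patients randomized to early cooling, the RhinoChill catheters should be placed and cooling initiated immediately", which places the start of device exposure during CPR and before ROSC.

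**The concern.** An endpoint that counts all adverse events needs the same rule for counting them in both arms. Here one of the three routes onto the form is a judgement that the event looks device-related. Control patients have no device, so the route is closed to them. The events named under it are mostly minor local signs, which can also follow airway handling, CPR or anticoagulation.

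Without a control rate collected on the same terms, the trial cannot say how many minor nasal and mucosal events are in excess of those of ordinary resuscitation and hospital care. Those who judge relatedness also know the allocation.

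**Working it through.** The plan states no adverse-event figure, so there is none to reproduce. The check is first textual, then illustrative.

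**1. Which arm can meet each route?**

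| Route in the recording rule | Severity threshold | Cooling arm | Control arm |
|---|---|---|---|
| Clinically significant | yes | yes | yes |
| Appears related to the RhinoChill | none | yes | no |
| Could potentially harm the patient | potential for harm | yes | yes |

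A minor event, neither clinically significant nor potentially harmful, has one route in the cooling arm and none in the control arm.

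**2. Recording rule against endpoint.** The endpoint is unfiltered and its clock starts with advanced life support. The rule is filtered and its clock starts at ROSC. They differ on which events count and on when counting begins.

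**3. Direction.** The device route alone adds minor events to the cooling arm. The ROSC start acts the other way: device use begins during CPR, so non-serious device events before ROSC, and all those in patients who never reach ROSC, fall outside the rule. No figure is given for either effect, so the sign of the sum cannot be computed.

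**4. Size of the device-route effect alone.** Let n be the admitted patients per arm, b the background rate of minor listed events (equal in both arms, with no device effect), a the share of them recorded in the cooling arm, and c the share recorded in the control arm.

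Spurious excess = n × b × (a − c)

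n = 150 comes from the Statistical analysis section; b = 3-10% is an assumption.

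- Worst case, a = 1 and c = 0: 150 × 0.03 = 4.5 and 150 × 0.10 = 15, so about 5-15 events.
- Half attributed to the device, a = 0.5 and c = 0: 2.25 to 7.5 events.
- Half attributed and a quarter of control events recorded through another route, a = 0.5 and c = 0.25: 150 × 0.03 × 0.25 = 1.1 to 150 × 0.10 × 0.25 = 3.75 events.

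**5. Effect on a comparison of patients with any event.** Suppose a proportion p in each arm has an event recordable in either arm. Of the rest, a proportion m in each arm has only a minor event that is recorded in the cooling arm alone. The true rates are then equal, but the recorded rates are p in the control arm and p + (1 − p)m in the cooling arm. With d = (1 − p)m, the chance of two-sided p < 0.05 is approximately Φ((d − 1.96 × SE0)/SE1), where SE0 uses the pooled rate and SE1 the separate rates.

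For p = 0.10, m = 0.10 and n = 150: d = 0.09, SE0 = √(2 × 0.145 × 0.855/150) = 0.0407 and SE1 = √((0.10 × 0.90 + 0.19 × 0.81)/150) = 0.0403. The chance is Φ(0.26), about 60%.

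| m (assumed) | Excess in points, p = 10-30% | Chance of p < 0.05, 150 per arm |
|---|---|---|
| 2% | 1.4-1.8 | about 5-7% |
| 5% | 3.5-4.5 | about 10-22% |
| 10% | 7-9 | about 25-60% |

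The larger excess and the higher chance belong to p = 10%. These figures cover the device route only and leave out the opposing loss of events before ROSC.

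**The case against.** The rule is one sentence for all patients and is not written by arm. Its bracketed list could be read as a fixed list of event types to be noted in anyone. The case report form is not shown, one is provided for each enrolled subject, and an article condenses the full protocol. This is a fair caution against saying that the control count is forced to zero. It does not remove the point, because the article itself states both a rule and an endpoint, and the two do not fit. If the list was meant for both arms, tying it to apparent relation to the device is the wrong wording.

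A reader might infer that control events are recorded only if clinically significant. The text does not support that: potentially harmful events are recorded in either arm, and a bleed in an anticoagulated control patient could qualify on either ground.

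A reader might also infer that the endpoint as a whole is biased against the cooling arm. That is not established either, because the ROSC start hides device events during CPR.

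The rhinoscopy difference is a lesser matter. The examination follows signs already seen, so it mostly describes an event already noted; only findings made solely at rhinoscopy add to unequal detection.

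Finally, this is a secondary endpoint, and the Statistical analysis section describes no formal test of it. Serious events go to the safety committee under one rule for all subjects. This limits the consequence to minor, non-serious events.

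**Conclusion.** The point holds in limited form. The recording rule and the all-adverse-events endpoint do not match, and minor nasal and mucosal events are ascertained unequally between the arms. The device route taken alone raises the cooling-arm count; the net direction over the endpoint is uncertain.

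The size rests on an assumed background of 3-10%. About 5-15 events per 150 admitted patients is a worst case: it requires every background event in the cooling arm to be recorded and none in the control arm. The base of admitted patients is itself an approximation, since the endpoint is not restricted to them.

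The documents do not support calling the safety comparison invalid as a whole. The serious-adverse-event endpoint and the primary endpoint are untouched. The wording should still be changed, because the correction is cheap and removes an avoidable difference in ascertainment.

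**What to change.** In Data safety management, replace the recording rule with one that applies identically in both arms. The listed events (nasal whitening, epistaxis, mucosal irritation or dryness, para-sinus emphysema, pleural effusion) and all other adverse events go on the same case report form checklist, regardless of severity or suspected relation. Relation to the device becomes a separate field and no longer decides whether an event is recorded.

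Leave rhinoscopy as planned. Exclude findings seen only at rhinoscopy from the between-arm comparison and report them descriptively for the cooling arm.

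This change equalises which events count. It does not settle when recording starts: the ROSC start of the rule and the endpoint's start at advanced life support must be reconciled as well.

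The cost is protocol and form wording, and a few more minor events recorded in control patients.

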## Discussion

The most common limitation in CA studies is the lack of either pre-hospital or in-hospital standardised protocols to manage these patients. This also applies to TH. Most studies on cooling after CA were limited to the in-hospital setting, where patients were treated after admission to the Emergency Department or ICU and evaluation of outcome is restricted to hospital discharge and corrected for several in-hospital factors [27,28]. This approach may of course create different confounders; indeed, pre-hospital factors have a significant impact on survival of resuscitated patients and the presence of different types of EMS may provide unbalanced quality of CPR and pre-hospital care that could later affect the measured outcomes [29,30]. On the other hand, pre-hospital studies generally lacked a standardised in-hospital management of these patients while post-resuscitation care can also substantially alter neurological recovery after anoxic injury [19,31]. Moreover, in some studies, cooling was also interrupted after hospital arrival, thus limiting its potential benefits [19]. These are all important issues to consider when discussing the optimal time to start TH after CA.

The importance of this trial is the comprehensive approach where the whole chain of factors and management of the patient is investigated. This is indeed the largest trial investigating a brain selective cooling approach, initiated in the pre-hospital setting, and involving numerous people in the treatment of such patients from the field until ICU admission. The rationale behind the PRINCESS study is to confirm the promising results observed in the PRINCE trial, although with the ambition to improve the management of the patients in terms of earlier initiation of cooling, limited cooling interruptions from the pre-hospital to the in-hospital setting, a standardised in-hospital management and a longer follow-up period for improved neurological evaluation. Importantly, we aimed to limit the number of centres to ensure that the use of TNEC and patients management should be as standardised as possible. The risk of having many centres with low inclusion rate and poor skills with Rhinochill use may influence the final results.

Few data are available on the optimal timing to initiate TH after CA. The PRINCESS study will test the effect of TNEC during CPR on patient neurologically intact survival when compared to standard in-hospital cooling. If brain selective cooling will improve brain recovery after anoxic injury, an important improvement in the pre-hospital management of such patients will be obtained.

## Abbreviations

ALS: Advanced life support; CA: Cardiac arrest; CPC: Cerebral performance category; CRF: Clinical report form; CPR: Cardiopulmonary resuscitation; DNAR: Do not attempt to resuscitate; EMS: Emergency medical service; etCO2: end-tidal carbon dioxide; IATH: Intra-arrest therapeutic hypothermia; ICU: Intensive care unit; OHCA: Out-of-hospital cardiac arrest; PEA: Pulseless activity; PEEP: Positive end-expiratory pressure; PI: Principal investigator; PFC: Perfluorocarbon; ROSC: Return of spontaneous circulation; SAE: Serious adverse event; SSEP: Somato-sensory evoked potential; TH: Therapeutic hypothermia; TNEC: Trans-nasal evaporative cooling; VF: Ventricular fibrillation; VT: Ventricular tachycardia.
